**Ethics and research integrity**

***Fundamental principle***

We will perform this trial in accordance with the Randomized Controlled Principle of trial design.

***Institutional Review Board (IRB)***

Prior to this clinical trial, the study will be reviewed by the IRB at Fourth Military Medical University School of Stomatology for a written approval.

***Ensuring human-rights***

We will comply with the Declaration of Helsinki and place maximum priority on ensuring human rights, welfare and the safety of the subjects. The protocol of this trial will be externally reviewed by anonymous independent ethical review committees to ensure no serious ethical concerns.

**Discussion**

Periodontitis is a chronic, infectious disease of the human periodontium that is characterized by the loss of supporting tissues surrounding the tooth, such as the PDL, cementum and alveolar bone. A major goal of periodontal therapy is the regeneration of the entire supporting structures of teeth. Although a number of treatment modalities are currently available, such as conventional treatments that mechanically remove the bacterial biofilm and the use of platelet-rich plasma, enamel matrix derivatives, and/or recombinant human growth factors that actively induce periodontal regeneration, clinicians continue to seek more predictable regenerative therapies that are less technique-sensitive, lead to fast tissue regeneration, and are applicable to the broad array of periodontal conditions encountered daily in the clinic. Recent evidence from animal models [20-29] and several small-scale pilot/feasibility studies [30-33] indicates that *ex vivo* cultured PDL cells may serve as powerful “tools” for periodontal therapy. Numerous animal studies have provided an overwhelming body of evidence that suggests that MSCs can be used for periodontal regeneration. As a consequence of these successful animal studies, the clinical application of stem cells for the regeneration of periodontal tissue has begun [16].

Thus, these data support the move from animal studies to human clinical trials. However, there are critical steps in moving the field towards human clinical utility. First and foremost, the safety and efficacy of these cell-based therapies has not been fully evaluated, and the risks of stem cell therapies have been underscored by several clinicians and researchers. Second, issues, such as cell delivery, cell immunogenicity, use of autologous cells or allogeneic cells, control of cell fates *in vitro* and *in vivo*, and cost-effectiveness are all important considerations that need to be addressed before this therapy can progress [39,40]. The next critical phase requires the identification of which tissues provide the most appropriate donor source and the systematic validation of specific MSCs that are reliable sources for periodontal cytotherapeutic use. Furthermore, the establishment of large-scale preparation facilities incorporating the stringent protocols of good manufacturing procedures will be an absolute necessity. Finally, regulatory agencies must define new criteria to evaluate the risk associated with specific stem cells and their differentiated progeny (reviewed in [39,40]). The purpose of this trial is to provide evidence to support the use of *ex vivo*-cultured cells to treat periodontitis and determine the best approach for treating this disease.

In the case of incurable and life-threatening diseases, such as diabetes, Parkinson’s, muscular dystrophy, Alzheimer’s, neural and cardiac diseases, and refractory systemic lupus erythematosus, cell-based therapy is more likely to be warranted and accepted by the government and patients [41,42]. However, periodontal tissue regeneration using cell therapy may not be economically viable or competitive with the currently available root canal therapies and dental implants. Due to the non-life-threatening nature of periodontitis, periodontal tissues are not a major target for stem cell-based regenerative medical research. Nevertheless, affected teeth are ideal for the evaluation of new therapies because the patients are not usually ill. Thus, if anything goes wrong with the treatment, the situation is far less likely to be life threatening. Furthermore, the accessibility of teeth facilitates treatments that do not require major surgery.

We expect to complete patient recruitment by December 2014 and anticipate that the results of this study will have implications for oral health care and facilitate improvements in the treatment of people with periodontitis. The results of this study will also allow us to determine if cell-based intervention is safe and effective for human dental use in clinical trials. These results may have important implications for the design of subsequent clinical trials and the development of sustainable, cost-effective cell-products for people with periodontitis.

This study will use central randomization, which is a strict and complete randomization method that ensures adequate concealment. The surgeon and the investigator who collect baseline and follow-up data will work independently in this trial. Throughout the entire trial, the patients are not aware of their group assignment. They will be told only that they will receive a periodontal surgery treatment that potentially includes cell products. This trial is a single-center randomized controlled study of approximately 30 patients that includes a 12-month follow up. This trial will be the first randomized controlled trial to address the effectiveness of cell therapy in combination with GTR and bone replacement for periodontitis.

In conclusion, stem cell therapy is a promising nascent therapy that may lead to the regeneration of lost periodontal tissue. Regenerative dentistry is at the forefront of the transition of basic science research to the clinical reconstructive arena. Although there are many issues that need to be resolved before stem cell therapies become commonplace, clinicians should continue to monitor the progression of these technologies.

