**Fourth Military Medical University**

**2011.06**

**Abstract**

**Background**: Periodontitis, which progressively destroys tooth-supporting structures, is one of the most widespread infectious diseases and the leading cause of tooth loss in adults. Evidence from animal studies indicates that stem cells derived from either bone marrow or the periodontal ligament (PDL) can be used in therapies for the regeneration of lost or damaged periodontal tissues. The aim of this clinical trial is to identify the safety of the clinical use of stem cells in periodontal therapy and to verify whether stem cells in combination with Bio-oss® are more effective than Bio-oss® alone in guided tissue regeneration (GTR) techniques for treating periodontal disease in human patients.

**Methods/Design**: In this protocol, we designed a single-center randomized trial to treat periodontal disease using GTR techniques and bovine-derived bone mineral (BDBM, Bio-oss®) with or without the incorporation of autologous periodontal ligament stem cells (PDLSCs). In total, approximately 30 periodontitis patients aged 18 to 65 years with a total of approximately 40 test teeth with periodontal intrabony defects and who satisfy our selection and exclusion criteria will be enrolled. These patients will be randomly assigned to either the Cell testing group (treatment with GTR and PDLSC sheets in combination with Bio-oss®) or the Control group (treatment with GTR and Bio-oss® without containing cells). During a 12-month follow-up, we will examine the extent of any adverse events related to the use of PDL cells. Moreover, the primary outcome is the magnitude of change in the alveolar bone height, and the secondary outcome measures are improvements in clinical attachment level (CAL), probing depth (PD), and gingival recession (GR).

**Discussion**: The results of this trial will assess the efficacy, safety and feasibility of using autologous PDLSCs to treat periodontal intrabony defects, and these data will provide primary clinical evidence for the future use of autologous stem cells in regenerative periodontal therapy.

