**Methods/Design**

**Overview**

***Purpose***

The purpose of this clinical trial is to confirm the safety of autologous stem cells in clinical periodontal regenerative surgery and clarify the efficiency of autologous periodontal ligament (PDL) stem cells to form cell sheets that can be used to regenerate periodontal tissue in periodontitis patients with deep intraosseous defects (>5 mm). This study is a single-center, randomized, controlled study (Figure 1) that was approved by the ethical committees of School of Stomatology, Fourth Military Medical University (2011-02) and registered in the ClinicalTrials.gov database (reference no. NCT01357785). The study will be conducted according to the Declaration of Helsinki, and we will obtain consent from all enrolled subjects with regards to participation in this trial and contribution of trial data for non-commercial purposes. The protocol of this trial was externally reviewed and approved by an anonymous independent ethical review committee to ensure no serious ethical concerns. This study is a randomized clinical trial that includes a test and control group for comparison and involves only one dental facility (Translational Research Team, School of Stomatology, Fourth Military Medical University). The clinical trial will be conducted according to the schedule shown in Figure 1.

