**Study Design**

Each patient will be examined by at least five independent principal investigators. Investigator 1 will perform a basic oral examination using a clinical inspecting apparatus and X-ray, check all of the inclusion and exclusion criteria, and ensure that the informed consents are signed by the patients at the Registration Center. Next, Investigator 2 will perform the pre-surgical treatments, re-check the inclusion and exclusion criteria, and extract the tooth/teeth that will be subjected to cell isolation by Investigator 4. Investigator 2 will select no more than 2 teeth (from different regions) to be investigated in each patient. Following the collection of baseline data from the selected tooth/teeth by Investigator 3, Investigator 4 will culture the cells, make the cell products, and create an allocation table consisting of 2 cases per block that will be allocated to the Control group (Bio-oss® only) and Cell group (Bio-oss® and cell sheets). According to this allocation table, a label indicating the corresponding group will be attached to each tooth; thus, each tooth will be randomly assigned to one of the two treatment groups. The maximum number of teeth from one patient will be 2. Hence, if one tooth is allocated to the Control group, the other will be automatically assigned to the Cell group. However, if a patient only has one tooth chosen for investigation, it has a fair chance of being allocated to either group. Once a tooth is assigned to a group, it will be kept in a secure locked drawer inaccessible to all other study personnel. All of the patients will receive oral hygiene instructions, a tooth cleaning and basic dental therapies if needed, such as cavity filling and occlusal adjustment. The periodontal surgery will be performed 4-5 weeks after these pre-surgical treatments. When the oral condition and cell products are both ready for surgery, Investigator 4 will be asked to give the assigned implants (Bio-oss® only or a combination of Bio-oss® and cell sheets) to the physician (Investigator 5), who will then perform the surgery. This procedure ensures that the randomization is not influenced by the physicians taking part in this study. Investigator 4 will record the patients’ details and number the envelope assigned to each tooth. Investigator 3 will perform the follow-up study (data collection, safety assessment, etc.) of the patient, and the blind will not be broken until this clinical trial is completed.

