**Patients and enrolment**

Patients with periodontitis visiting our dental institution will be requested to participate. This study will be conducted in compliance with Good Clinical Practice guidelines. Prospective patients who provide written informed consent will undergo clinical inspection and an oral cavity diagnosis. We will then select approximately 30 patients (approximately 40 testing teeth) who satisfy the selection and exclusion criteria described below (most of these criteria were chosen from previous similar periodontal clinical trials [34,35]).

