**Adverse events**

***Definition***

An adverse event is any unfavorable and unintended sign (including an abnormal laboratory finding), symptom, or disease that is temporally associated with the use of the investigational cells whether or not it is considered to be related to the investigational cells. We will examine the extent of any adverse events.

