**Statistics**

This study will be performed using a per-protocol analysis. In this analysis, all of the randomized teeth will receive at least one therapy, but teeth that do not receive treatment will be excluded (modified per-protocol analysis). The last-observation-carried-forward method will be used for the per-protocol analysis. The missing data points will be input into the post-baseline follow-up visits from the last observation available for each patient. For analysis, we will use SAS version 8.2 software (SAS Institute Inc., Cary, North Carolina, USA). The per-protocol set analysis will be performed for the primary outcome. The baseline between-group comparisons within age and clinical examination indices will be performed using independent group *t* tests. The between-group comparison of sex will be performed using Fisher’s exact probability test. The changes in clinical examination indices will be tested using a repeated-measures analysis of variance. The level of statistical significance will be set at *p*<0.05.

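### The protocol sets out to confirm the safety of the cells, but about 20 cell-treated patients can only reveal common harms and cannot exclude uncommon ones

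*Protocol*

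**What the plan says.** Safety is the first stated aim. The Purpose section of the protocol reads: "The purpose of this clinical trial is to confirm the safety of autologous stem cells in clinical periodontal regenerative surgery". The Discussion carries this forward to the conclusions: "The results of this study will also allow us to determine if cell-based intervention is safe and effective for human dental use in clinical trials". The Abstract is softer: "The aim of this clinical trial is to identify the safety of the clinical use of stem cells in periodontal therapy".

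On size, Patients and enrolment says: "We will then select approximately 30 patients (approximately 40 testing teeth) who satisfy the selection and exclusion criteria". Study Design adds: "The maximum number of teeth from one patient will be 2". Under that section, a patient with two study teeth has one in each group, and a single study tooth has an equal chance of either group.

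On how safety will be judged, the adverse event definition says only: "We will examine the extent of any adverse events". Events are graded for severity and assessed for seriousness and relation to the cells, and blood, urine and serum antibody tests are done. The protocol gives no tolerable event rate, margin or confidence bound for safety, and no reason why this size is enough to settle it.

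**The concern.** Confirming safety is a claim about what has been ruled out. It needs a number of exposed patients large enough that a good result excludes an event rate that would matter. The protocol makes the claim and fixes the size, but does not connect the two.

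What is at stake is the conclusion the trial may draw. The Discussion expects the results to inform later trials, and it also acknowledges that the safety of these therapies is not yet fully evaluated. If the stated purpose is confirmation, a clean record in a small exposed group can carry more weight than it should.

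**Working it through.** **Inputs.** About 30 patients and 40 teeth (Patients and enrolment). At most two teeth per patient, two-tooth patients split between groups, single teeth allocated with equal chance (Study Design). The protocol gives no event rate and no calculation behind the size, so there is no figure of its own to reproduce. The event rates in step 3 are assumptions, shown as a range.

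**Step 1: patients exposed to cells.** With P patients and T teeth, T − P patients have two teeth and 2P − T have one. Every two-tooth patient receives cells, and so do about half of the one-tooth patients:

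exposed = (T − P) + (2P − T)/2 = T/2

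- P = 30, T = 40: 10 two-tooth patients + 20/2 = 20 exposed, leaving 10 control-only.
- T = 38 to 42 gives 19 to 21 exposed. With T = 40, P = 28 or P = 32 still gives 20.

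**Step 2: what zero events would exclude.** The exact upper limit for 0 events in n patients is 1 − α^(1/n).

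| Exposed patients | One-sided 95% (α = 0.05) | Two-sided 95% (α = 0.025 in the upper tail) |
|---|---|---|
| 18 | 15.3% | 18.5% |
| 20 | 13.9% | 16.8% |
| 22 | 12.7% | 15.4% |

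For n = 20: 1 − 0.05^(1/20) = 0.139 and 1 − 0.025^(1/20) = 0.168.

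**Step 3: what the trial would see.** The chance of no event in 20 patients is (1 − p)^20.

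| Assumed true rate p | Chance of zero events | Chance of at least one |
|---|---|---|
| 1% | 82% | 18% |
| 5% | 36% | 64% |
| 10% | 12% | 88% |

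**Step 4: the exposure that a firmer statement would need.** For zero events to exclude a rate p at one-sided 95%, n must be at least ln(0.05)/ln(1 − p). That is 59 exposed patients for p = 5% and 299 for p = 1%. These numbers show the scale of the gap; they are not a proposed sample size.

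**The case against.** **The document as a whole is modest.** The Discussion sentence asks whether the intervention is safe; it does not announce that it is. The Abstract offers early clinical evidence, and the Discussion calls the therapy nascent and looks to further trials. This stands as a reading of tone, and the strong verb is in the Purpose section alone. But the softer passages do not withdraw it, and undertaking to determine whether the cells are safe still promises an answer that this exposure cannot give.

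**Twenty patients are informative.** This stands. Step 3 gives an 88% chance of seeing at least one event at a true rate of 10%. Events are also judged individually for severity, seriousness and causality, and laboratory changes are followed up. A common harm would probably show. The limit concerns what a clean result excludes.

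**The safety analysis may be in a statistical analysis plan.** It may, and lists of event counts or intervals for laboratory changes are ordinary content for one, so their absence here is not the point. No analysis method can make about 20 exposed patients confirm safety while the protocol's purpose says that it will.

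**A stronger reading to avoid.** A reader might infer that zero events, or a non-significant difference between groups, will be taken as proof of safety. The protocol has no such rule. Its significance level ("The level of statistical significance will be set at" p<0.05) is in a paragraph on baseline comparisons and on changes in clinical examination indices; Fisher's test is named only for sex, and no between-group test of adverse events or blood values is named. It also sets no power or type II error target. Power figures for safety tests would therefore describe analyses that the protocol does not plan, and none are used here.

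**Conclusion.** The point holds as a mismatch between a stated property and the design. The Purpose section says the trial will "confirm the safety of autologous stem cells in clinical periodontal regenerative surgery", but with about 20 exposed patients even a spotless result leaves true event rates up to 13.9% (one-sided 95%) or 16.8% (two-sided 95%) compatible with the data. A true rate of 5% would produce no events in 36% of such trials.

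The upper limits rest only on the exposed count, which follows from the protocol's own numbers and allocation rule, and on treating patients as independent. They change little between 18 and 22 exposed patients. The 36% depends on an assumed rate, since the protocol gives none.

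This does not show that the trial is too small for an early study, that any planned analysis is wrong, or that the sponsor will report safety as confirmed. The fault is in the claim.

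**What to change.** In the Purpose section, and correspondingly in the Discussion, restate the safety objective as a preliminary estimate of the incidence of adverse and serious adverse events per cell-treated patient, reported with an exact 95% upper limit. State in advance that with about 20 exposed patients zero events excludes only rates above about 14% (one-sided) or 17% (two-sided), and that zero events alone will not be taken as confirming safety.

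This costs a few sentences and the calculation of an exact limit. It needs no extra patients, visits or tests. The downside is a more modest safety claim.

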***Study Products***

Bio-Oss® and Bio-Guide® (Geistlich Pharma AG, Volhusen, Switzerland) and PDL cell sheets (cells obtained from a patient’s tooth/teeth; see inclusion criteria) will be produced at the Research and Development Center for Tissue Engineering (Fourth Military Medical University, [name]) using a standardized procedure (see section 5.1. cell products). Both transplants (Bio-oss® only or Bio-oss®/cell sheets) will be prepared (ready for immediate use) by the laboratory researchers, and Investigator 3, who will perform the follow-up study, will remain blinded to the treatment conditions.

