**Safety assessment**

***Observation of subjective symptoms and objective findings***

Medical findings for both the oral cavity and whole body will be confirmed by interview and visual inspection.

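### In two-tooth patients the pairing rule makes cell exposure certain, so the safety assessor's blind covers which tooth received cells but not the patient's exposure

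*Protocol*

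**What the plan says.** **Allocation (Protocol, Study Design).** The unit of randomisation is the tooth: "The maximum number of teeth from one patient will be 2". For a patient with two study teeth, "if one tooth is allocated to the Control group, the other will be automatically assigned to the Cell group". For the others, "if a patient only has one tooth chosen for investigation, it has a fair chance of being allocated to either group". The Abstract, by contrast, speaks of patients: "These patients will be randomly assigned to either the Cell testing group" or to the Control group.

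**Who assesses safety (Study Design, Study Products).** Investigator 3 collects the baseline data on the selected tooth or teeth and later carries out follow-up, which Study Design says includes the safety assessment, with the blind kept until the trial ends. Study Products adds: "Investigator 3, who will perform the follow-up study, will remain blinded to the treatment conditions".

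**What safety covers (Safety assessment).** "Medical findings for both the oral cavity and whole body will be confirmed by interview and visual inspection". Blood, urine and serum antibody tests are added. Under Evaluation of adverse events, the investigators judge whether an event is related to the cells.

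**What patients know (Discussion).** Patients are described as unaware of their group throughout. "They will be told only that they will receive a periodontal surgery treatment that potentially includes cell products". No distinction is made between patients with one and with two study teeth.

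**The concern.** Safety is a stated purpose of the trial, and much of it is observed on the patient rather than the tooth. A whole-body symptom or a laboratory value cannot be attributed to one of two teeth. The exposure that matters for it is whether the patient received cells at all, and the pairing rule settles that for every two-tooth patient before any label is drawn.

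An assessor who knows the rule and the number of study teeth therefore knows that these patients are exposed. The knowledge runs one way: no control-only patient can be recognised as unexposed. Interview findings, and any relatedness judgement informed by them, are open to expectation in the known-exposed patients and not in the same way in the rest. A report that called the systemic safety assessment blinded would claim a property the design lacks for these patients.

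The patient information raises a second, smaller matter. The Discussion describes one message for everyone, worded as a possibility, although for two-tooth patients cells become a certainty.

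**Working it through.** The protocol gives no figure for exposed patients, so there is none to reproduce. The check is a count.

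**Inputs**
- Patients P: about 30; teeth T: about 40 (Patients and enrolment; also the Abstract).
- At most 2 teeth per patient (Study Design).
- Probability that a patient is assigned cells: 1 with two teeth, 0.5 with one (Study Design).

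**Formulas**
- Two-tooth patients x and one-tooth patients y satisfy x + y = P and 2x + y = T, so x = T − P and y = 2P − T.
- Expected cell-exposed patients = x + y/2 = T/2.
- Expected control-only patients = y/2.

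**Planned totals (P = 30, T = 40)**
- x = 40 − 30 = 10; y = 60 − 40 = 20.
- Exposed = 10 + 20/2 = 20; control-only = 20/2 = 10.
- Exposure can be deduced from the tooth count in 10/30 = 33% of patients, which is 10/20 = 50% of the exposed.
- Teeth split 20:20, but patients are expected to split 20 exposed to 10 unexposed.

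If each one-tooth patient were an independent fair draw, the number of the 20 given cells would lie between 6 and 14 with probability 0.96. The blocks of two in the allocation table would tend to narrow that. The 10 two-tooth patients are exposed either way.

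**Sensitivity to the approximate totals** (assumed: 28 to 32 patients, 38 to 42 teeth)

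| P | T | Two-tooth | One-tooth | Exposed | Control-only | Two-tooth share of patients | Two-tooth share of exposed |
|---|---|---|---|---|---|---|---|
| 32 | 38 | 6 | 26 | 19 | 13 | 19% | 32% |
| 30 | 40 | 10 | 20 | 20 | 10 | 33% | 50% |
| 28 | 42 | 14 | 14 | 21 | 7 | 50% | 67% |

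**What each person can infer**
- *Investigator 3, two-tooth patient:* the tooth count is known from baseline and the rule is in the protocol, so exposure is known. Which tooth received cells is not.
- *Investigator 3, one-tooth patient:* exposure remains an even chance.
- *Radiographic examiners:* they compare teeth, and knowing that one of two received cells does not say which. The primary outcome is untouched.
- *Patients:* on the Discussion's account they are not told the rule, so they cannot make the inference.

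**Timing of the patient information.** In Study Design, Investigator 1 sees that consent is signed, and Investigator 2 then selects the teeth. At signing, the number of study teeth is open and cells are a possibility for everyone. Once two teeth are chosen they are certain, and the protocol mentions no update.

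**The case against.** **The masking statements can be read at tooth level.** Study Design randomises teeth, so the blind and the treatment conditions may mean only which implant went where, and that stays masked. This is a fair reading, and it is the one the protocol should state. As written, the statements carry no such limit and the same sentence of Study Design extends them to the safety assessment. The Abstract's wording about assigning patients also encourages the wider reading.

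**The consequence may be small.** Much of the systemic safety data is laboratory values, which expectation hardly affects. Relatedness is given to the investigators in general, with no claim that this judgement is blinded. The Statistics section plans no between-group test of adverse events. All of this stands, and no size of bias can be derived. What remains is interview and inspection, and any part Investigator 3 has in relatedness, in about 10 patients.

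**Stronger readings that the protocol does not support.** A reader might infer three things:
- *That patient masking fails.* It is not shown to. Patients told only what the Discussion describes do not know the pairing rule.
- *That the patient message is wrong from the outset.* Consent precedes tooth selection, so it can be accurate when signed.
- *That it contradicts the consent undertakings under Purpose and under Patients and enrolment.* Those sections say consent will be obtained, not what patients must be told. The consent pages are not among the material at hand, so any fuller explanation there cannot be seen.

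**Conclusion.** The point holds in a limited form. For about 10 of 30 patients, about half of the roughly 20 expected to receive cells, the blind stated in Study Design and Study Products protects tooth identity but not patient-level cell exposure. Whole-body safety findings in these patients are known-exposure data. Over the assumed range of totals the number is 6 to 14. The Discussion's account of what patients are told stops fitting these patients once two teeth are selected.

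This rests on three assumptions: the planned totals are roughly met, two-tooth patients are treated as allocated, and Investigator 3 knows the allocation rule. The protocol does not say the rule is withheld from Investigator 3. The radiographic primary outcome and the roughly 20 one-tooth patients are outside the point. It calls for correcting a masking claim and separating some safety data; it does not show that the safety results are biased.

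**What to change.** 1. In Study Design, Study Products and the Discussion, state that in two-tooth patients masking is at tooth level: which tooth received cells is concealed, but the patient's exposure is not concealed from anyone who knows the rule.
2. Report whole-body adverse events and their judged relatedness separately for two-tooth patients, labelled as known-exposure data. Claim masked systemic safety assessment for one-tooth patients only.
3. Reconcile the patient information described in the Discussion with the pairing rule. For example, say at consent that if two teeth are selected one of them will receive cells, without saying which.

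Randomisation, treatment and tooth-level masking do not change. The work is protocol and patient-information wording and one extra split in the safety tables.

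There are two downsides. The masking claim becomes more modest. Two-tooth patients who understand that they will receive cells may also bring some expectation of their own to interview-based safety reports; reporting them separately makes this visible but does not remove it.
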